## Abstract

**Introduction:**

Obesity affects over a quarter of the UK population and can lead to serious health issues. NHS Specialist Weight Management Services (WMS) offer treatments including lifestyle advice, psychological support and medications, but access and availability vary by region. Although around 4 million people could be eligible for NHS Specialist WMS annually, capacity is limited to 35 000, severely limiting overall access for those who need it. While digital technology has started to be used in WMS, more evidence is needed to confirm its long-term effectiveness, acceptability and cost-effectiveness. This study explores the use of Gro Health W8Buddy, a digital platform and app providing remote Specialist WMS. It aims to determine the long-term health benefits of remote WMS pathway Gro Health W8Buddy compared with standard NHS WMS delivered in hospitals, and to improve patients access to services.

**Methods and analysis:**

The study is a real-world evaluation with observational data collection. We will recruit 450 study participants from four NHS specialist WMS who will choose either standard NHS WMS or the digital pathway Gro Health W8Buddy. Participants are being given the option to choose their pathway to generate real-world evidence. We will measure and analyse health outcomes including weight loss, time taken to be treated and cost-effectiveness, at 18 months and follow up at 24 months for later analysis (outside of this core funding). We will gather experiential data from patients and healthcare professionals through surveys, observation and interviews.

**Ethics and dissemination:**

Ethical approval has been obtained from NHS Health Research Authority (HRA) and Health and Care Research Wales (HCRW) (Supplementary Figure 3) (REC reference: 25/EM/0147). Our findings will be disseminated through academic publications, conference presentations and stakeholder engagement.

**Trial registration:**

ISRCTN89168871; Pre-results.

STRENGTHS AND LIMITATIONS OF THIS STUDYThe study is structured around four distinct work packages, each employing a unique research methodology.The digital intervention has been co-created with NHS staff and patients and is backed by research.This research methodology has been shaped by patient and public involvement input from all four NHS sites.The study methods enable real-world evidence to be generated by allowing participants to choose their own pathway of care. Therefore, we will provide credible evidence for further roll-out of digital technology in weight management services across the UK.Allocation is not randomised, which may lead to more participants in digital care or vice versa. This approach inevitably introduces complexity into the analysis, but it is a design choice advised by patient contributors.

## Introduction

### Background

In the UK, a quarter of adults live with obesity, with higher rates among people from Black and Asian ethnic groups and people living in the most deprived areas.^1^ People living with obesity are at increased risk of chronic diseases including type 2 diabetes mellitus (T2DM) and cardiovascular disease as well as at risk of shorter life expectancy.^2^ Treatment of obesity cost the NHS £6.5bn in 2022, with an associated ill health annual full cost of £58bn.^3^ The NHS and Office for Life Sciences (OLS) identified treatment and prevention of obesity as one of its healthcare missions.^4^

A tiered approach to weight management exists in the UK. Tiers 1 and 2 are delivered in community and primary care. Tier 3 is delivered by specialist Weight Management Services (WMSs) which are often based in a hospital setting. WMS comprises multidisciplinary teams who provide dietetics, psychology and consultation by specialist doctors. Tier 4 services include bariatric surgery.^5^ In the UK, National Institute for Health and Care Excellence (NICE) recommends that people with a body mass index (BMI) over 40 kg/m^2^ or over 35 kg/m^2^ with medical problems (eg, T2DM, hypertension) are eligible for referral to WMS.^6^ However, there is substantial geographical and service variation, with many areas lacking access to services.^7^

Outcomes from traditional face-to-face WMS are mixed, with 50% of patients in most NHS WMS achieving a 5% wt loss over 6–12 months according to a recent review.^8^ Retention rates are low (<55%) and there is little long-term (>12 months) data on sustainability of weight loss.^8^ WMSs have limited capacity for just 35 000 patients,^9^ yet 4 million people are eligible for services. This represents a significant capacity issue.^10^ Due to these access constraints, only 3.13% of this population receive a referral to WMS.^9^ There is also marked regional variation in service design and accessibility.^7^ High-risk groups such as individuals from deprived areas in the UK often face barriers to accessing in-person Tier 3 services due to costs of transport and having support with childcare.^11^ This is important to note as the obesity prevalence is 37.4% in deprived areas compared with 19.8% in less deprived areas.^12^

In March 2023, NICE recommended the obesity medication semaglutide (Wegovy (TM)) for people accessing WMS.^13^ Additionally, tirzepatide was recommended for obesity treatment from December 2024.^14^ These treatments represent a step change in tier 3 WMSs and are part of the government-backed pilot to widen access to this medication with the use of digital technology.^15^ However, guidance on the incorporation of digital technology to address how to safely incorporate the drugs remains unclear. We aim to fill the gap with this study.

Digital technology for managing chronic disease, including obesity, is expanding rapidly in the NHS.^16^ Acceptability of digital technology for weight loss is high in both community and WMS settings, which is important to note considering the current barriers to WMS uptake and accessibility.^17–20^ However, effectiveness varies. Evidence shows weight loss ranging from 13% at 4 months (digital+meal replacements)^21^ to 7.6% at 12 months (digital+coaching).^22^ A community-based digital weight management intervention recorded 5% wt loss at 2 years in 18% of users.^20^ According to the evidence, there is a gap and need for further digital weight management research to investigate standard and digital care, alongside the integration of pharmacotherapy (eg, semaglutide) and the use of a multidisciplinary team.^21^ Currently, the evidence on the digital divide created by digital technology for weight management is lacking.^23^ Therefore, innovative approaches are needed in the NHS WMS to reduce health inequality, address efficiency, increase capacity and improve access to pharmacotherapy for obesity.

As a result of the above evidence, we co-created a digital support tool *Gro Health W8Buddy* (W8Buddy) with a digital company Diabetes Digital Media (DDM) to provide digital technology to deliver NHS WMS.^7^ W8Buddy provides personalised WMS to support patients to achieve their self-selected health goals and support weight loss with real-time remote monitoring. The creation of W8Buddy was supported by an *HEE Topol Digital Fellowship* and *NHS Clinical Entrepreneur scheme*.^24^ Evidence has shown that W8Buddy helps to reduce weight, improve glycaemic control and well-being among people living with obesity, overweight or with T2DM.^25 26^ W8Buddy was endorsed by *NICE Early Value Assessment* for Digital Technologies in Specialist Weight Management in October 2023.^27^

Our initial 1-year evaluation of 412 patients showed that 220 patients using W8Buddy (version 1—information resource) alongside traditional WMS lost significantly more weight (0.75 kg/month) than 192 patients using traditional WMS.^28^ Since then, W8Buddy has been adapted to provide a fully remote WMS. This study aims to provide longer term real-world evidence (RWE) of the clinical and cost-effectiveness of the adapted W8Buddy in the NHS.

#### Research question

What is the long-term (18-month) impact on clinical outcomes, including health-related quality of life (QoL) and cost-effectiveness of W8Buddy with and without weight management medication and lifestyle support to people living with obesity, compared with WMS standard care?

### Objectives

To generate longitudinal evidence of the clinical and cost-effectiveness of the W8Buddy from four NHS WMS, University Hospital Coventry & Warwickshire (UHCW), University Hospitals Birmingham (UHB), London Luton Trust (LLT) and Hywel Dda University Health Board Trust (HDUHBT), using the digital pathway W8Buddy.To generate sufficient evidence to satisfy NICE guidance requirements.^27^To understand the process of implementation and use of W8Buddy within WMS.To create a manual for safe incorporation of a digital pathway delivering weight management medication into existing WMS across the UK.To make recommendations for how we can optimise existing infrastructure of WMS to improve ongoing RWE generation.

## Methods

### Study design

Multisite prospective comparative observational cohort study with embedded cost-effectiveness analysis and process evaluation. Comprising four work packages to assess the following: (1) Set up, Patient and Public Involvement and Engagement (PPIE) and Stakeholder engagement, (2) Clinical impact, (3) Health economic impact and (4) Process evaluation.

### Eligibility criteria to enter WMS in the UK

Inclusion criteria reflect the eligibility of people to enter the clinical services participating in this research, including services with additional eligibility criteria restrictions (subject to local processes that may differ slightly). However, while individual services may have further restrictive criteria, which is reflective of many WMSs, all participants are included within:

Adults aged 18 years and aboveClass 2 obesity (BMI ≥35 kg/m^2^) with at least 1 medical complication (eg, pre-diabetes, T2DM); or patients with obesity class 3 (BMI ≥40 kg/m^2^), without any complications.

The eligibility criteria for access to Tier 3 WMS for adults from South Asian, Chinese, other Asian, Middle Eastern, Black African or African-Caribbean background have BMI cut-offs of 37.5 kg/m^2^ without comorbidities.

#### Exclusion criteria

Pregnant or breastfeeding.T1DM.End-stage renal disease (eGFR <15, receiving renal replacement therapy).Active or untreated alcohol or drug dependency.Decompensated liver disease.History of anorexia, undergoing treatment or awaiting treatment for DSM-V classified eating disorder.Severe mental health disease, including acute mental health crisis or self-harm in the last 12 months.Unstable mental health disease, including unstable personality disorder, schizophrenia and bipolar disorder.Unwilling or unable to commit to participation across the length of the research study.Patients targeting bariatric surgery within the length of the research study.Participating in another weight management research intervention.Participating in the diabetes remission programme.

### Study setting and sites

This study will run at four NHS sites (UHCW, UHB, LLT, HDUHBT). Standard care differs across the recruiting sites, including the mixed provision of obesity medication. Sites without medication as standard care will be noted as the digital pathway without medication.

### Patient and public involvement

A W8Buddy PPI Group has been established with a minimum of four PPI Representatives with lived experience of WMS from each site. Potential PPI representatives have been identified through WMS teams at each participating site and obesity charities. Those interested in joining the groups are invited to meet with the PPIE Lead and/or UHCW PPIE Team to discuss the opportunity, commitment required and support offered and to find out about their experience and background. PPI representatives selected represent the diverse population of the WMS users in each area. The Group meets quarterly to ensure ongoing input from people with lived experience, including identifying outcome measures that are meaningful for people with obesity, providing feedback on participant-facing documents, working on creating local pathways and training materials. The PPI Group will also shape analysis and risk mitigation, may take part in conducting semistructured interviews as part of qualitative research, and support dissemination of findings afterwards. This research methodology has been shaped by PPI input from all four NHS sites.

### Sample size calculation

We will collect weight data at baseline and a minimum of three occasions during the study, for both pathways. Powering the study to show that the digital pathway is non-inferior to the standard of care pathway, with a difference less than 4 kg, at 90% power and a two-sided 5% level, gives a sample size of approximately 180 participants. Further assuming a correlation between the repeated weight measurements in the range 0.2–0.5, which previously collected data suggests is reasonable,^28^ based on a longitudinal mixed model/repeated measures Analysis of covariance (ANCOVA) gives a total sample size of 360. Conservatively assuming 20% loss during follow-up, the target sample size is 450.

Given the current widespread use of the digital (W8Buddy) intervention at the lead centre (UHCW), the control (standard of care; SC) intervention at this site will be different from that offered at the other sites. For this reason, we plan to characterise the control intervention at UHCW as a ‘hybrid’ digital intervention. We will aim to recruit sufficient participants (ie, 360) at the three other sites (UHB, LLT, HDUHB) to fully power the study for the planned comparison between the digital and standard of care groups. Additionally, we will collect data from the ‘hybrid’ digital intervention at UHCW to augment and further refine the primary analysis.

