### Assessment and management of risk

Risks relate to data management/reporting across four sites and management of the digital pathway delivered by DDM. The latter is assured by DDM. Table 2 lists these. Further information on data management and flow can be found in online supplemental table 2, adverse events (online supplemental table 2) and online supplemental figure 1.

10.1136/bmjopen-2025-109111.supp5Supplementary data

10.1136/bmjopen-2025-109111.supp1Supplementary data

**Table 2 T2:** Assessment and management of risk

Data reporting	Not reporting data by participants, mitigated by regular support via the app or contact from the research team if not completing surveys.
Data protection	As with any online service, proper data handling is assured by high security data storage in line with NHS Digital policies. Data from NHS sites transferred to analytical partner using secure pathways.
Delivery	The site research team will oversee all participants, including those accessing digital pathway. The first contact for any queries for participants on the digital pathway will be the digital provider, and if the query is not resolved, the research site team will be contacted. The project will be managed by PH and AG via weekly WP meetings between sites and project manager, with monthly oversight by each site PI. Three-monthly meetings of the PPIE group will ensure ongoing input from patients. Annual project steering committee meetings will review risk registers.
Imbalanced recruitment	More patients opting for digital rather than standard of care pathway (or vice-versa), mitigated by over-recruiting standard of care (or digital) patients and adjusting as per analysis plan using propensity-weighted approach, purposive sampling and ongoing monitoring of recruitment, communication to sites, telephone and offline packs as another option for those choosing digital pathway.
Engagement with the digital pathway	Low engagement from high-risk/target groups resulting in lower enrolments and participation from those most in need of the service. Mitigated by patient-friendly resources, onboarding support and a research nurse at each site to act as a point of call.

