#### Primary and secondary outcome analysis

The primary analysis will compare temporal changes in weight for the W8Buddy and standard care group, from baseline to completion of follow-up (at 18 months), using longitudinal mixed effects regression models. The effectiveness of the W8Buddy will be quantified by differences in rates of weight change compared with standard of care during follow-up. All the secondary outcomes will be analysed individually with longitudinal mixed effects models.

For all analyses, we will consider adjusting for a range of demographics and clinical characteristics (eg, age, gender, ethnicity, Index of Multiple Deprivation/Welsh Index of Multiple Deprivation, comorbidities, NHS site, mode and distance of travel and other confounders identified using Directed Acyclic Graphs with stakeholders PPI members and members of the steering committee)^31^ using propensity-weighted longitudinal mixed models. We expect the fixed effects to be demographics and clinical characteristics as mentioned above and the random effects to be the sites and individuals. A sensitivity analysis using distance to NHS site as an instrumental variable^32^ will also be conducted to assess the assumption of no unmeasured confounders.

The comparison between the hybrid intervention and both the standard of care and fully digital intervention will be an unpowered secondary analysis, that we hope will offer additional insights and help to characterise the magnitude of intervention effects from the primary analysis.

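### The stated 90% power at 360 participants is not shown for the comparison planned: self-chosen arms with propensity weighting

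*Protocol article*

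**What the plan says.** The section on sample size calculation sets a non-inferiority aim for the digital pathway, with a margin of 4 kg. The first step of the calculation, "at 90% power and a two-sided 5% level, gives a sample size of approximately 180 participants". The section then brings in a correlation between repeated weights of 0.2 to 0.5 and reports that a calculation "based on a longitudinal mixed model/repeated measures Analysis of covariance (ANCOVA) gives a total sample size of 360". Allowing for 20% loss gives 450. The section's second paragraph treats 360 participants at the three sites other than the lead centre as enough to power the digital versus standard comparison fully.

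The comparison itself is described elsewhere. Under screening, recruitment and consent, eligible patients choose their own pathway. The strengths and limitations list warns: "Allocation is not randomised, which may lead to more participants in digital care or vice versa". The section on primary and secondary outcome analysis uses longitudinal mixed models and says the team will consider adjusting for confounders "using propensity-weighted longitudinal mixed models". In Table 2 of the risk section, the row on imbalanced recruitment lists over-recruitment of the smaller arm, purposive sampling, recruitment monitoring and "adjusting as per analysis plan using propensity-weighted approach".

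**The concern.** Every increase in the count has a stated cause: 360 is attributed to the repeated-measures model and 450 to loss. Neither cause is imbalance or weighting. At a fixed total, unequal arms lower precision, and variable propensity weights usually lower it further. The stated 90% therefore does not describe the analysis the article sets out.

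The stake is a non-inferiority study that ends inconclusively although the digital pathway is truly non-inferior. The article intends its results to support NICE review and national adoption. A head count of 360 could look on target while the smaller arm's effective size is well below 180.

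Table 2 adds a smaller problem. It offers propensity weighting as a remedy for imbalanced recruitment. Weighting addresses confounding; it does not give back the precision lost when one arm is small.

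**Working it through.** **Inputs from the article:** margin 4 kg; power 90%; two-sided 5% (one-sided 2.5% for non-inferiority); totals 180, 360 and 450; loss 20%; correlation 0.2 to 0.5; baseline plus at least three weights.

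**Assumptions, because the article gives no figure:** true difference 0; the SD; the split between arms; the variance inflation from weighting, written DE and applied equally to both arms.

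**Reproducing the plan's figures.** 360/(1 − 0.20) = 450, which agrees. The 180 and 360 cannot be checked without an SD, so I solve for it. With z = 1.960 + 1.282 = 3.242 and n per arm, SD = (4/3.242) × √(n/2):
- 180 in total (n = 90): SD = 8.28 kg.
- 180 per arm, 360 in total (n = 180): SD = 11.71 kg.

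**The step from 180 to 360.** For ANCOVA on the mean of r = 3 follow-up weights, the variance factor is (1 + (r − 1)ρ)/r − ρ². It lies between 0.42 and 0.44 for ρ from 0.2 to 0.5, which would cut 180 to about 75 to 80. The doubling fits either 180 being a per-arm figure or a factor 1 + (3 − 1) × 0.5 = 2. The article does not say which, if either.

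**Power for the planned comparison.** For digital share p at N = 360:

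power = Φ(4 / (SD × √(DE × (1/n₁ + 1/n₂))) − 1.960)

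If 360 is exactly the 90% requirement at 1:1, this reduces to Φ(3.242 × √f − 1.960) with f = 4p(1 − p)/DE. For 70:30 and DE 1.25, f = 0.84/1.25 = 0.672 and power = Φ(2.657 − 1.960) = 75.7%.

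| Split | DE 1.0 | DE 1.25 | DE 1.5 |
|---|---|---|---|
| 50:50 | 90.0% | 82.6% | 75.4% |
| 60:40 | 88.8% | 81.1% | 73.7% |
| 70:30 | 84.4% | 75.7% | 67.9% |
| 75:25 | 80.2% | 70.9% | 63.0% |

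At 70:30 with DE 1.25, holding 90% would take 360/0.672 = 536 evaluable, or 536/0.8 = 670 recruited.

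If 180 in total was the requirement (SD 8.28 kg), f doubles:

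| Split | DE 1.0 | DE 1.25 | DE 1.5 |
|---|---|---|---|
| 50:50 | 99.6% | 98.4% | 96.3% |
| 70:30 | 98.8% | 96.4% | 92.9% |
| 75:25 | 97.8% | 94.4% | 90.0% |

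**Is a DE of 1.0 to 1.5 a reasonable range?** As an illustration, take inverse-probability weights, a normal propensity score on the logit scale with SD 0.5, 0.75 or 1.0 (c-statistic about 0.63, 0.69, 0.74) and Kish effective sizes. Then f is 0.938, 0.860, 0.757 at 50:50 and 0.764, 0.673, 0.559 at 70:30. Dividing 4p(1 − p) by f gives DE of about 1.07, 1.16, 1.32 at 50:50 and 1.10, 1.25, 1.50 at 70:30. These figures ignore any precision gained from covariates in the outcome model.

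**The case against.** The strongest reply is that no deficit has been demonstrated. A reader might infer that the design fails to deliver 90% power for its own analysis. The article does not support that. It gives no SD, and it does not say whether 180 is per arm. Read literally as a total, 180 leaves 360 with 96.4% power at 70:30 and DE 1.25, and 90.0% at 75:25 and DE 1.5. This part of the objection stands. It does not close the matter, because the text presents 360 as the output of the repeated-measures model and not as a reserve for imbalance or weighting.

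Second, Table 2 does plan to over-recruit the smaller arm and to monitor recruitment. That also stands, and over-recruitment is the measure aimed at a small arm. It has no figures, however. It must also fit within a total of 450 whose arms the participants choose, and it does nothing about weighting loss.

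Third, the outcome analysis section only says that adjustment will be considered, and the weight type is left open. So the size of the weighting loss cannot be fixed from this article. Still, Table 2 refers to propensity weighting as part of the analysis plan, and the Discussion says that planned analyses will adjust for differences between arms. An unweighted comparison is not what the article leads one to expect.

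Fourth, an article condenses, and a split or a design effect may appear in the full protocol. The point here is not that a detail is absent. The article gives a chain of inputs and a power claim, and that chain does not match the comparison described in the same article.

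**Conclusion.** The 90% power is not shown for a comparison of self-chosen arms with propensity weighting. If 360 is the 90% requirement and the true difference is 0, imbalance alone gives 88.8% at 60:40 and 84.4% at 70:30; an assumed design effect of 1.25 gives 82.6% at 1:1 and 75.7% at 70:30. Near-equal arms with weak predictors of choice would cost little. If 180 in total was the requirement, 360 holds at least 90% up to a combined loss factor of 2.

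The splits and design effects are my assumptions, and the SDs are back-calculated. The conclusion is that the stated power is unsupported for this analysis, not that the study is underpowered. Listing propensity weighting as a remedy for small arms in Table 2 should be corrected on either reading.

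**What to change.** In the sample size section:
- Define 360 as the effective sample size after weighting, not a head count.
- State the SD and the basis of the step from 180 to 360, including whether 180 is per arm.
- Replace the single 90% with power over a stated range, for example a digital share of 50 to 75% and a weighting design effect of 1.0 to 1.5, keeping the target at 450.

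In Table 2, in the row on imbalanced recruitment:
- Keep propensity weighting as confounding control only and rely on over-recruitment for a small arm.
- Monitor effective sample size per arm as well as head count.

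The type of weight can be left to the analysis plan. The cost is a short recalculation and some rewording, with no extra participants; the stated power may become less favourable.

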Eating disorders	Weight loss can trigger or exacerbate eating disorders. For individuals with a history of eating disorders, weight loss medications could potentially be misused in a harmful way. This is mitigated through patient completion of psychological assessments, medication eligibility assessment and approval for medication from the MDT team providing the patient’s care. On the digital pathway, regular reviews with a pharmacist and psychologist ensure medication is not mismanaged and appropriate for the patient. Signposting and referral back to the GP will be provided to any patients who display signs of disordered eating. On the standard of care pathway, local protocols will be followed.
Engagement with the standard of care pathway	High drop out from the standard of care pathway: there is a high drop out from the standard of care service in tier 3 Weight Management, resulting in high loss to follow-up. This will be mitigated by having a dedicated research nurse who will contact patients to ensure they complete all data collection in a timely fashion. Additionally, participants in the standard of care will receive vouchers to compensate them for the additional surveys they will be asked to do.

GP, general practitioner; PI, principal investigator; PPIE, Patient and Public Involvement and Engagement; WP, work packages.

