#### Missing data

Patterns of missing data/discontinuation will be reported and assessed if missingness was at random or provided useful information on treatment efficacy.

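### The 20% loss allowance is labelled conservative against the article's own evidence, and the 360 recruits at the three powered sites carry no loss allowance at all

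*Protocol article*

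**What the plan says.** **Sample size calculation.** The aim is to show that the digital pathway is "non-inferior to the standard of care pathway, with a difference less than 4 kg". The first step, "at 90% power and a two-sided 5% level, gives a sample size of approximately 180 participants", is followed by a repeated-measures step "assuming a correlation between the repeated weight measurements in the range 0.2–0.5", which "gives a total sample size of 360". Then: "Conservatively assuming 20% loss during follow-up, the target sample size is 450". The second paragraph of that section sets 360 as the number to recruit at the three sites other than the lead centre, and says this gives the digital versus standard-care comparison its full power.

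**Background**, on traditional face-to-face services: "Retention rates are low (<55%) and there is little long-term (>12 months) data on sustainability of weight loss".

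**Assessment and management of risk (Table 2)**, row on engagement with standard care: "there is a high drop out from the standard of care service in tier 3 Weight Management, resulting in high loss to follow-up". The same row names the mitigation: a dedicated research nurse who chases data collection, and vouchers. The recruitment section sets the vouchers at £10 per completed survey, for standard care.

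**Statistical analysis plan.** Comparisons are primarily as-started. Little or no switching or discontinuation is expected in the W8Buddy group. Detail is left to a later SAP.

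**Missing data.** Patterns will be reported and "assessed if missingness was at random or provided useful information on treatment efficacy".

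**The concern.** A conservative allowance is one that the available evidence says is unlikely to be exceeded. The only retention figure in the article implies service loss above 45%, and the article itself links service drop-out in standard care to loss of study data. The expectations also differ by arm, while the allowance is a single overall figure. If loss runs above 20%, the study does not have the 90% power it states. In a non-inferiority design the cost is a wider interval that may fail to exclude 4 kg.

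The three-site figure raises a second issue. The number needed after loss (360) is used there as the number to recruit, so the stated power would require no loss at those sites.

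A smaller point is that the missing-data sentence implies the data can show whether missingness was at random. Observed data cannot separate missing at random from missing not at random, and a likelihood-based mixed model relies on the former.

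**Working it through.** **Inputs from the article:** 360 needed before loss, 20% loss, target 450, 90% power, two-sided 5%, 360 recruits at three sites, service retention below 55% (loss above 45%).

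**Assumptions, because the article gives no figure:** a 1:1 split (pathway is the participant's choice), 360 analysable taken as exactly 90% power (no SD is stated, so 360 cannot be re-derived), and only complete cases counted. For the 450 rows, all recruits are treated as contributing to the comparison.

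**1. The plan's own figure.** 360/(1 − 0.20) = 450. Reproduced exactly.

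**2. Power under other losses.** With z(0.975) + z(0.90) = 1.960 + 1.2816 = 3.2415,

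power = Φ(3.2415 × √(Neff/360) − 1.96), where Neff = 4·n1·n2/(n1 + n2)

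and n1, n2 are the analysable numbers per arm. Starting from 225 per arm:

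| Standard-care loss | Digital loss | n1 | n2 | Overall loss | Neff | Power |
|---|---|---|---|---|---|---|
| 20% | 20% | 180 | 180 | 20% | 360 | 90.0% |
| 30% | 10% | 157.5 | 202.5 | 20% | 354.4 | 89.5% |
| 30% | 30% | 157.5 | 157.5 | 30% | 315 | 85.8% |
| 45% | 0% | 123.75 | 225 | 22.5% | 319.4 | about 86% |
| 45% | 10% | 123.75 | 202.5 | 27.5% | 307.2 | 85.0% |
| 45% | 20% | 123.75 | 180 | 32.5% | 293.3 | 83.3% |
| 45% | 45% | 123.75 | 123.75 | 45% | 247.5 | 76.7% |

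Worked example (45% and 20%): Neff = 4 × 123.75 × 180/303.75 = 293.3. Then 3.2415 × √(293.3/360) − 1.96 = 0.966, and Φ(0.966) = 83.3%.

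If standard care alone loses 45%, overall loss is 22.5% even with no digital loss, already above the allowance.

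**3. The three sites.** 360 × 0.80 = 288 analysable. Then 3.2415 × √(288/360) − 1.96 = 0.939, and Φ(0.939) = 82.6%. To leave 360 analysable at 20% loss, these sites would need 360/0.80 = 450 recruits, which is the target for the whole study.

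**4. Missing-data sentence.** No arithmetic applies. Two mechanisms that agree on the observed data can differ only in the unobserved values, so no assessment of observed patterns settles which one holds.

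**The case against.** The strongest reply is that the two percentages measure different things. Retention below 55% describes people staying in ordinary face-to-face services, whereas the 20% is loss of study data. The analysis is as-started, local teams can reach health records, people unable to commit to the study's length are excluded, and the risk-table entry describes the problem before the nurse and vouchers act. The retention figure does not cover the digital arm, where little discontinuation is expected.

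Most of this stands. An overall loss near 20% is possible: 30% in standard care and 10% in digital gives exactly that, with 89.5% power. A reader might infer that power is overstated outright, or is 77%. The article does not support that, because 76.7% needs 45% loss in both arms. Complete-case figures are also at the low end for a given loss, since people with partial follow-up contribute to the mixed model. The base of 360 is itself unverifiable. If 180 were the true total requirement, 450 recruits with 45% loss would still give about 97%.

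The reply does not rescue the label. The article gives no figure for the effect of the nurse or the vouchers, and its own risk table ties service drop-out to loss to follow-up. Low digital discontinuation concerns treatment. Digital support runs for 52 weeks, whereas the endpoint is at 18 months, so complete digital weights are not assured.

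Three other stronger readings should be resisted:

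- **Three-site power of 67.1%.** This is 45% loss applied to 360 recruits. It mixes two problems, because the missing allowance already lowers power to 82.6% at the plan's own 20% loss.
- **A bias of known size towards non-inferiority.** The article says nothing about how the weights of those lost would differ. If more standard-care participants are missing and they did worse, observed standard care looks too good, which works against the digital arm.
- **A gap for want of an imputation or tipping-point analysis.** That is normal SAP content and is expressly deferred. The missing-data sentence does acknowledge that missingness may be informative.

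**Conclusion.** The point holds in a limited form. The article's own evidence does not support calling 20% conservative, and 90% power should not be stated without a condition on loss. Under the assumptions above, power for 450 recruits is about 83–86% if standard care alone loses 45%, 76.7% in the extreme case of 45% in both arms, and close to 90% if losses are 30% and 10%. Because retention is given as below 55%, 45% is the least loss that figure implies. Whether study weights will follow it is not known.

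The three-site shortfall does not depend on that dispute. At the plan's own 20% loss, 360 recruits leave 288 and about 82.6% power, on the same 1:1, complete-case basis.

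The missing-data sentence is a minor matter of wording.

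**What to change.** 1. In the sample size section, delete the word conservatively, or justify 20% separately for each arm, with evidence on what nurse contact and vouchers achieve for study weights.
2. State power over 20–45% loss by arm, for example as the table above, with the SD and split on which it rests.
3. For the three non-hybrid sites, either state the power that 360 recruits give after loss (about 82.6% at 20%), or restate the recruitment number with the allowance applied (450 at 20%).
4. In the missing-data section, say that missing at random cannot be verified from the observed data and will be examined by sensitivity analysis, with the details in the SAP.

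Items 1, 2 and 4 cost wording and a less favourable power statement. Item 3 costs the same if power is restated. It needs 90 more recruits at those sites (450 − 360) only if the team chooses to keep 90% power there.
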